**Objectives**

Comparing 2-arms, we will assess the efficacy of the LifeBuoy app in reducing suicide ideation among young people, as measured by the Suicidal Ideation Attributes Scale (SIDAS; [9]), relative to a placebo attention control condition. Changes in suicidal ideation will be assessed by comparing the intervention to the attention placebo control condition at 0-days (baseline, T0), 30-days (T1), 60-days (T2), and 120-days (T3). In addition, the trial will be used to:

- Examine the efficacy of a digital engagement on app adherence (measured by the number of modules / activities / exercises completed; number and frequency of app log-ins; total time spent on the app) by comparing 2-arms: LifeBuoy + engagement strategy versus LifeBuoy-only at T1, T2, and T3.
- To determine whether the LifeBuoy app reduces incidents of suicide attempt and non-suicidal self-injury relative to the placebo attention control condition at T1, T2, and T3.
- To assess whether the LifeBuoy app reduces depression and anxiety symptoms relative to the placebo attention control condition at T1, T2, and T3.
- To examine whether the LifeBuoy app + engagement condition reduces suicidal ideation relative to the LifeBuoy-only condition at T1, T2, and T3.

**Investigational Products**

LifeBuoy. The Lifebuoy app is a mobile app developed by researchers at the Black Dog Institute. It is a fully automated, self-guided program for young people experiencing mild-to- moderate symptoms of suicidal ideation. The app has been developed using a person-centered approach, to understand and accommodate the perspectives of young people who will use the intervention. Participants will download the app from the App Store or Google Play onto their personal smartphones. Once the app is downloaded, it will not require internet connection; internet connectivity will only be required to upload usage and adherence data to UNSW servers. The app contains seven learning modules derived from third wave CBT, and incorporates wise mind principles (distress tolerance, emotion regulation/mindfulness, interpersonal effectiveness) through interactive learning exercises to help young people develop strategies and skills for managing emotions and distress. Participants have access to the app until the end of the trial (120 days). Each module is expected to take 5 to 10 minutes to work through. The user will be directed to each module linearly.

**Follow-up Schedule**

All participants will be asked to complete self-report questionnaires at T1 – T3.

**Roles and Responsibilities**

As outlined by NHMRC Guidance on “Safety monitoring and reporting in clinical trials involving therapeutic goods” (2016), the roles of the DSMB will be to assist in:

- safeguarding the interests of study participants
- ensuring that definitive and valid results are produced which will reliably inform future healthcare decisions enhancing the credibility of the trial.
- These roles will be achieved by examining the data accumulated during the progress of the trial, ensuring risks and benefits are monitored, and that the trial remains safe for participants. The role of the committee is to review data completeness, adverse events, outcome data (unblinded if there is good reason for this) and to recommend to the trial committee whether the study requires modification.
- Recommendations will be made to the TSG, which, if appropriate, will be shared by the trial team with the Sponsor and the HREC.

Following each assessment point, the DSMB will:

- Review aggregate subject data related to safety, attrition, withdrawals, data integrity and overall conduct of the trial and discuss via telephone conference.
- Provide recommendations to continue, modify or terminate the trial.
- Maintain records of all activities.
- Comply with conflict of interest guidelines and confidentiality guidelines as described in this charter.

The Investigators will:

- Assure the proper conduct of the study according to the study protocol and relevant research guidelines;
- Assure collection of accurate and timely data;
- Compile and report data for the DSMB report at the end of each assessment period (trial manager and data officer);
- Monitor the project email inbox;
- Promptly report potential safety concern(s) to the DSMB;
- Communicate with regulatory authorities, e.g. HREC, in a manner that maintains integrity (e.g., blinding) of the data, as necessary.

**DSMB Membership**

**Composition**

DSMB membership for the trial will be established prior to recruitment commencing and an updated charter listing the DSMB members will be submitted to the Ethics Review Committee.

**Selection of the Chair**

The Chair should have previous experience of serving on a DSMB and experience of chairing meetings, and should be able to facilitate and summarise the DSMB discussions.

**DSMB Meetings**

**The first meeting**

Prior to recruitment commencing, the DSMB members will review and ratify this charter and form an understanding of the protocol and study endpoints.

The members should review this charter and form an understanding of the protocol and study endpoints. Meetings will take place at an appropriate regularity decided by the DSMB committee. The DSMB will also meet if evidence from other research groups suggests potential for risk.

**Reporting**

As this is a trial of an mhealth preventive intervention, and not a medicine or treatment, it is regarded as being in the lowest risk category, type A, with risk comparable to standard medical care. All Serious Adverse Events (SAEs) will be regarded as non-expedited (ie. only to be reported at the next DSMB meeting), unless the SAE is both unexpected and possibly related directly to participation in the trial, in which case it will be reported to the DSMB via email within 24 hours as well as other agencies. For this 6-week low intensity app-based DBT intervention, it is anticipated that all SAEs that are possibly related to trial participation will be reported. In the event of uncertainty, the TSG should default to reporting the SAE to the DSMB.

**Responsibilities of the Data Officer**

The data officer will be responsible for producing the closed session report to the DSMB, and assist the trial manager with the open session report. The main purpose of this role is to ensure that the Investigator team remain blind to study outcome data. No interim analyses will be performed unless explicitly required by the DSMB with a strong rational. The process for communicating the report is as follow:

1. The data officer will extract unblinded data and prepare reports for the DSMB (using the attached shell) and disseminate the report one week prior to the scheduled meeting.
2. The data officer will be responsible for extracting both confidential and non-confidential data from the trial data collection platform.
3. The data officer will participate in the DSMB meetings to take the members through the report if required.
4. These discussions will remain confidential and not communicated to the trial team.
5. Responsibilities of the Chief Investigator and Trial Steering Group (TSG)
6. The trial leads and trial manager must be available to attend open sessions.
7. Other TSG members (see membership details on p. 5) are not required to attend, but may attend if they wish to.

**Safety Analyses**

Suicidal behaviour (ideation, attempts, and NSSI)

- Suicidal ideation, as measured by % scoring >20 on the SIDAS
- A suicide attempt during the trial identified at all follow up surveys: “Since the last LifeBuoy study survey, how many times have you made an attempt to kill yourself in which you had some intent to die?” >0 (T1 – T3) or ad hoc self-report by participants to research study email.
- Non-suicidal self-injury during the trial identified at all follow up surveys: “Since the last LifeBuoy study survey, how many times have you injured yourself on purpose without suicidal intent (i.e., intentional, self-inflicted damage to the surface of the body but with no intent to die)?” >0 (T1 – T3) or ad hoc self-report by participants to research study email.
- Serious adverse events (including all events requiring medical intervention).
- Enrolment data, intervention completion data, attrition data, adverse event data, and other administrative data.

The TSG cannot access the unblinded data for suicidal ideation, attempt, or NSSI as these are outcome measures and will be shared only in a closed session.

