Efficacy of the engagement strategy: the other primary objective is to explore whether participants who receive LifeBuoy + a digital engagement strategy report higher rates of app usage (measured in terms of the number of modules completed, number of app logins, and total time spent on the app) relative to the LifeBuoy-only condition. This trial will answer important questions about whether, and what, digital strategies improve user engagement, addressing key knowledge gaps in the digital health field. Previous research has shown that technology-based strategies can potentially improve user engagement [14]. However, a plausible reason why many such strategies fail is because they do not sufficiently address the needs of users and are thus not well-received [15]. Moreover, few studies have examined the efficacy of social media (e.g., Instagram) and blog posts in promoting greater engagement with DMHIs. More specifically, we will examine the efficacy of a digital engagement strategy – designed to optimise use of the LifeBuoy app – on app adherence (measured in the following ways: number of modules / activities / exercises completed; number and frequency of app log-ins; total time spent on the app) by comparing 2-arms: LifeBuoy + engagement strategy versus LifeBuoy-only at 0-days (baseline, T0), 30-days (T1), 60-days (T2), and 120-days (T3).

Secondary outcomes

1. To determine whether the LifeBuoy app reduces incidents of suicide attempt and non-suicidal self injury relative to the control condition at T1, T2, and T3.
2. To assess whether the LifeBuoy app reduces depression and anxiety symptoms relative to the control condition at T1, T2, and T3.
3. To examine whether the LifeBuoy app + engagement condition reduces suicidal ideation relative to the LifeBuoy-only condition at T1, T2, and T3.

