In this trial a Serious Adverse Event (SAE) is o one or more of the following events and the event is not related to the trial intervention:

1. A participant reporting a suicide attempt or NSSI that requires medical care at any follow-up assessment time point.
2. If we become aware of a death of a participant during the trial, for any reason, this will also be considered a serious adverse event.

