| (If yes to the past 30 days)  In the most severe suicide attempt in the past 30 days: | - Select all that apply - | No care was needed (0)  I attended the hospital, but without physical injury and left without being admitted (1)  I attended the hospital with a physical injury but left without being admitted (2)  I was admitted to hospital without physical injury (3)  I was admitted to hospital with physical injury (4) |
| How long have you been experiencing suicidal thoughts?  *Baseline only* | --- select ---- | 3 months or less (1)  Up to 12 months (2)  More than 12 months (3)  More than two years (4)  More than five years (5) |
| At what age did you first experience suicidal thoughts?  *Baseline only* | (free numerical response) | Participant to type in the number |
| Have you ever injured yourself on purpose *without suicidal intent* (i.e., intentional, self-inflicted damage to the surface of the body *with no intent to die*)  *Baseline only* | --- select ---- | No (0)  Yes (1) |
| (If yes) How many times have you injured yourself on purpose in the past 12 months?  *Baseline only* | (free numerical response) | Participant to type in the number |
| (If >0) How many times have you injured yourself on purpose in the past 30 days? | (free numerical response) | Participant to type in the number |
| (If past 30 days more than 0) In the most severe self-injury over the past 30-days (please select one): | --- select ---- | No medical care was needed (0),  I treated the injury myself (1),  I attended a medical clinic or hospital and left without being admitted (2),  I was admitted to hospital (3) |

[Patient Health Questionnaire-9] (PHQ-9)

| Over the last **2 weeks**, how often have you been bothered by the following problems? | Not at all | Several days | More than half the days | Nearly every day |
| --- | --- | --- | --- | --- |
| Little interest or pleasure in doing things | 0 | 1 | 2 | 3 |
| Feeling down, depressed, irritable, or hopeless | 0 | 1 | 2 | 3 |
| Trouble falling asleep, staying asleep, or sleeping too much | 0 | 1 | 2 | 3 |
| Feeling tired, or having little energy | 0 | 1 | 2 | 3 |
| Poor appetite, weight loss, or overeating | 0 | 1 | 2 | 3 |
| Feeling bad about yourself — or feeling that you are a failure, or that you have let yourself or your family down | 0 | 1 | 2 | 3 |
| Trouble concentrating on things, such as reading the newspaper or watching television | 0 | 1 | 2 | 3 |

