**Flagging procedure**

**1)** At each survey timepoint (baseline, 30-days, 60-days, and 120-days) three items indicates risk of suicide. When a selection is made indicating a concerning level of suicidal thinking (SIDAS score >20), a suicide attempt during the trial, or NSSI requiring medical care during the trial, an automated alert system is triggered, where an automated email is sent to the participant asking if they would like to receive a phone call from the team clinical psychologist during business hours (9:00 to 17:00 AEST) within the next 3 working days. This email will also include a list of crisis contact numbers for support.

*“Hi there,*

*Thanks so much for signing up to participate in the study and for completing the latest survey. We noticed that your responses on the survey indicate a recent self-harm event or severe current suicidal thoughts. If you would like to receive a phone call from our clinical psychologist during business hours (9:00 to 17:00 AEST) within the next 3 working days, please click ‘reply’ to this email or send a new email request to [contact]*

*If you’ve had a tough time with your mental health lately, we encourage you to talk to a local doctor or mental health professional about how you’re feeling. If you would like to know where to get some immediate help, here are some suggestions:*

- *Lifeline: [name]*
- *Kids Helpline :[name]*
- *Suicide Callback Service: [name]*

*For 24-hour advice on what to do and who to contact, don’t hesitate to visit HealthDirect (https://www.healthdirect.gov.au) or call them at [name]).*

*If you feel in danger or that you might hurt yourself, do not hesitate to call Emergency Services on 000.*

*Warm regards*

*The LifeBuoy team”*

(*Note:* at the completion of each survey all participants will be shown a screen with the same abovementioned support contacts).

**2)** If a flagged participant indicates they would like a call back, the team clinical psychologist ([name]) will contact the participant via phone as soon as possible. This discussion will centre around making sure the young person is supported in their family and/or community and identifying how they can access the services they need. If the participant expresses distress in relation to using the app or answering the assessment questionnaires, they will be reminded of their right to withdraw from the trial without penalty or the need for explanation.

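### The follow-up self-harm items, read literally, do not cover an overdose without intent to die, so such events are not reliably ascertained as SAEs

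*Protocol*

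**What the plan says.** The DSMB Charter, under Safety Analyses, gives two behaviour items for T1 to T3. The attempt item asks "how many times have you made an attempt to kill yourself in which you had some intent to die". The self-injury item asks about deliberate injury without suicidal intent and then defines it, by an i.e., as "intentional, self-inflicted damage to the surface of the body but with no intent to die". For both, the Charter also accepts an unprompted email from the participant. The same list then includes "Serious adverse events (including all events requiring medical intervention").

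Four other parts of the protocol use the same two constructs:

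- Types of Safety and Monitoring defines an SAE as "A participant reporting a suicide attempt or NSSI that requires medical care at any follow-up assessment time point"; the only other listed event is death.
- Serious Adverse Reaction puts the question on whether the study contributed only to participants who report one of those two events.
- The Flagging procedure acts on "a concerning level of suicidal thinking (SIDAS score >20"), or on "a suicide attempt during the trial, or NSSI requiring medical care during the trial, an automated alert system is triggered". Trial Stopping Guidelines repeats these three triggers.
- Secondary objective 1 asks whether the app "reduces incidents of suicide attempt and non-suicidal self injury relative to the control condition at T1, T2, and T3".

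Outcome measurement surveys has its own set of self-injury questions. A lifetime question, marked as baseline only, carries the limit "intentional, self-inflicted damage to the surface of the body". A later 30-day count does not repeat that limit. A question on medical care follows a positive 30-day count.

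**The concern.** One item needs intent to die and the other is confined to the body surface. Intentional self-harm without intent to die that leaves the surface intact, such as an overdose, poisoning or ingestion, lies between them. A participant who answers both items as worded would enter zero twice, even after a hospital stay.

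What is at stake is mainly safety ascertainment. Participants are enrolled because of recent suicidal thoughts, and the DSMB is asked to judge harm from these counts. Trial Design states that all assessments are electronic self-report with no outcome assessors, so no clinician interview would recover an event that the items miss. Some respondents may stretch the self-injury item to fit an overdose and others may not, and nothing in the survey would show which they did.

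**Working it through.** There is no figure to reproduce. The check follows one case, a hospital-treated overdose without intent to die, through each part of the protocol that could record it.

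1. **Attempt item (Charter).** It requires some intent to die. Not met. An ambivalent overdose with some intent would count here, so the gap concerns acts with none.

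2. **Self-injury item (Charter).** The stem, deliberate injury without suicidal intent, could include an overdose. The i.e. then restricts it to the body surface. Not met if the definition is applied; met only if the respondent answers from the stem and ignores it.

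3. **Survey appendix.** The 30-day self-injury count has no surface limit of its own and is not marked as baseline only. Its display condition refers to a 12-month count, which in turn depends on the surface-limited lifetime question. Both of those are baseline only. The protocol does not say whether at T1–T3 the 30-day count is shown to everyone, shown according to baseline answers, or replaced by the Charter item. None of these versions names overdose or poisoning.

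4. **Medical-care questions (survey appendix).** They appear only after a positive 30-day attempt or self-injury count. A participant who enters zero for both is not asked about hospital care.

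5. **Other survey items.** The substance-use scale asks how often prescription medicines were misused, not whether this was self-harm or needed care. The last PHQ-9 item asks about thoughts. Neither records the event.

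6. **SAE definition.** Under Types of Safety and Monitoring the case is neither an attempt nor NSSI as the item defines it, so it does not qualify. Under the Charter's Safety Analyses it does, because it needed medical intervention. The same event therefore has two classifications.

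7. **Relatedness question.** It is asked only after a reported attempt or medically treated NSSI. Not reached.

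8. **Alerts.** The two behaviour triggers are not met. The SIDAS trigger is independent of them and may still be met. Its questions concern suicidal thoughts and closeness to an attempt, so a non-suicidal overdose does not by itself raise the score, and answering never to the opening item sets the total to zero. Estimated flag and call-back rates reports 259 of 455 flagged in the first LifeBuoy trial: 259/455 = 56.9%, leaving 196/455 = 43.1% not flagged. A SIDAS flag leads to an email offer; it records no event and does not bring up the relatedness question.

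9. **Volunteered report.** The email route is written into the attempt and self-injury bullets. It could bring other events to light, but only if the participant chooses to write.

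Taken together, the Charter includes this event among SAEs, but no scheduled question is worded to collect it.

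**The case against.** The best defence is that several routes remain open. The Charter's SAE wording covers the event, and the general adverse event definition is broad enough to include it. SIDAS above 20 raises an alert whatever the behaviour items say, and every participant sees support contacts after each survey. The 30-day count in the survey appendix carries no surface limit, and the stem of the Charter item is broad.

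Much of this stands. A reader might infer that such events are lost from SAE reporting altogether, or raise no alert. The documents do not support that: the event is an SAE under the Charter, the person may be flagged through SIDAS, and some respondents may report it under a broad reading. What remains is that none of these routes dependably records the event.

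The defence is also right on efficacy. Secondary objective 1 names suicide attempt and NSSI. Leaving out non-suicidal overdose limits that construct but does not contradict it.

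A reader might further infer that the under-count pulls the arm comparison toward no difference. That does not follow in general. If a share *s* of true events is captured in both arms, with no false positives, the observed risks are *s*·p1 and *s*·p0. Their ratio is still p1/p0; the difference becomes *s*(p1 − p0), which is smaller, and precision falls. If capture differs by arm, the error could go either way. The documents give no basis for choosing among these.

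**Conclusion.** The concern holds as a matter of safety ascertainment. Read literally, the T1–T3 items do not cover intentional self-harm without intent to die that spares the body surface. The SAE definition in the protocol body, the relatedness question and the behaviour-based triggers rest on those items, while the Charter sets a wider SAE scope that no survey item serves. Such events are not reliably ascertained as SAEs.

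The conclusion depends on respondents applying the written definition and on the Charter wording being the one used at follow-up; if the 30-day count is asked of everyone without the surface limit, the gap narrows but does not close. The documents give no rate for medically treated non-suicidal overdose, so the number of events at issue cannot be stated, and any count would rest wholly on assumed rates. The NSSI secondary outcome is not shown to be wrong.

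**What to change.** At T1–T3, word the self-injury item, or add one item, to cover any intentional self-harm without intent to die, including overdose or poisoning. Add one tick for the method and attach the existing medical-care follow-up. Keep damage to the body surface as a separate category, so that the NSSI secondary outcome is unchanged and stays comparable with baseline.

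Then reconcile the text:

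- the SAE definitions in Types of Safety and Monitoring and in the Charter's Safety Analyses;
- the wording and display conditions of the self-injury items in the Charter and in Outcome measurement surveys, stating which are used at follow-up;
- the matching text in Serious Adverse Reaction, Trial Stopping Guidelines and the Flagging procedure.

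Whether the wider item should feed an alert, and how alerts are then managed, is for the sponsor to decide.

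The cost is a small survey change with an ethics amendment, and one extra tick for participants who report self-harm.
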